### Aims

• To establish the vitamin D status of South Asian women living in Auckland, NZ.

• To investigate the effectiveness of vitamin D supplementation in improving insulin sensitivity in women with hypovitaminosis D who have demonstrated insulin resistance, and/or lipid profiles in those with dyslipidaemia.

• To investigate the effect of vitamin D supplementation on bone marker ratios in women who have hypovitaminosis D.

## Method

The study consists of two phases: Phase one included initial recruitment and screening, phase two included recruitment of selected individuals into the vitamin D intervention trial (Figure 1).

**Figure 1 F1:**
[figure not shown]
Study design of the SURYA Study.

Phase one provided the opportunity for a comprehensive description of the population group with respect to general health, anthropometry, diet and other lifestyle factors. The majority of the phase one data were collected during one visit of the participant to either the Massey Human Nutrition Research Unit or Mount Roskill Surgical and Medical Centre. Participants were weighed and measured, blood samples taken, blood pressure and aural temperature measured, then the participant was given breakfast. During breakfast the medical history form was completed and checked and the diet diary explained.

### Participants

It was calculated that 42 subjects would be required for each arm of the trial to demonstrate a significant difference at 80% power and 5% significance. Power calculations were based on the results of a lifestyle intervention which achieved a reduction in HOMA-IR of 0.98 [28], and derived from Margetts and Nelson [29].

Women were invited to participate in the study through advertisements in suburban and Auckland newspapers, and Indian media such as television, radio and newspapers. Posters and leaflets were distributed in a number of venues around Auckland such as General Medical Practices with high numbers of South Asian patients, clubs, and temples. A number of South Asian social and community groups were given presentations about the study by the researchers.

A short television documentary on a channel popular with Indian viewers elicited the greatest response of all the methods used. However, the most effective form of promotion was word-of-mouth. A relatively small group of supportive women from the South Asian community promoted the study and were instrumental in the successful recruitment of 250 women.

### Inclusion/exclusion criteria

Women had to be 20+ years and of South Asian origin; either the subject, both parents or all grandparents must have been born on the Indian sub-continent i.e India, Pakistan, Bangladesh, Sri Lanka – generally referred to as South Asia.

Volunteers were excluded if suffering from significant renal dysfunction, major systemic illness, or diabetes requiring medication. Use of 25(OH)D_3 _supplements exceeding 1000 IU/day (i.e. prescription dose), or any form of calcitriol (1, 25(OH)_2_D_3_) were also exclusion criteria.

Additional inclusion criteria for the intervention trial were low vitamin D (<50 nmol/L) and a HOMA-IR (insulin resistance) measurement of >1.93 or hyperinsulinaemia (FPI >13 mIU/L) or hyperglycaemia (FPG 5.6 – 7.2 mmol/L) or a triglyceride/HDL-C ratio >3.0. HOMA-IR >1.93 was based on the upper quartile determined in the Chennai Urban Population Study-7 [30]. A triglyceride/HDL ratio >3.0 has been shown to be a surrogate marker for early insulin resistance in overweight/obese people [31].

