### Hypotheses

• There is a high prevalence of hypovitaminosis D in South Asian women living in Auckland, New Zealand.

• Supplementation of vitamin D in subjects who have demonstrated insulin resistance and vitamin D deficiency will result in an improvement in markers for metabolic syndrome.

• Supplementation of vitamin D in subjects who have demonstrated vitamin D deficiency will result in an improvement in bone marker ratios in favour of bone mineralisation.

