## Discussion

The information that was obtained from the screening phase of this study provided a valuable and unique insight into this rapidly increasing group of migrants entering New Zealand. It was not the intention during this phase to conduct a cross-sectional study and there was no attempt to recruit in a fully randomised way. Indeed, such recruitment in any specific, ethnic minority within a large population would be highly problematic. However, the 250 women who participated in phase one of the Surya Study represent approximately 0.5% of the total number of South Asian women living in New Zealand. Distribution in terms of country of origin reflected that of the entire population as reported in the 2006 census [24]. Level of education, although higher than the New Zealand national average, was as expected of a newly migrant population given New Zealand's immigration requirements for high educational standards [37].

As far as we are aware, there has been no other randomised, placebo-controlled, double-blind trial investigating the effect of vitamin D supplementation on insulin resistance and other markers of metabolic syndrome. If this trial is successful, it will provide another clue about the aetiology of type 2 diabetes, and the opportunity to reduce one of the many risk factors.

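### Hypothesis 1 and aim 1 claim the vitamin D status of South Asian women in Auckland, but phase one can describe only eligible volunteers, whose entry depended on vitamin D intake

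*Protocol article*

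**What the plan says.** The Hypotheses section states "There is a high prevalence of hypovitaminosis D in South Asian women living in Auckland, New Zealand", and the first item under Aims is "To establish the vitamin D status of South Asian women living in Auckland, NZ". Neither is limited to volunteers or to women meeting entry criteria.

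The Method section describes the first stage thus: "Phase one included initial recruitment and screening". Under Inclusion/exclusion criteria the general exclusions come first: "Volunteers were excluded if suffering from significant renal dysfunction, major systemic illness, or diabetes requiring medication". The next sentence adds the use of vitamin D "supplements exceeding 1000 IU/day (i.e. prescription dose), or any form of calcitriol". Only after that does the section turn to the trial: "Additional inclusion criteria for the intervention trial were low vitamin D (<50 nmol/L"), followed by the metabolic criteria.

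Under Participants, recruitment ran through media, posters, leaflets and community presentations, and "the most effective form of promotion was word-of-mouth". The Vitamin D intervention section reports 250 women screened, of whom 116 qualified for phase two.

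The Discussion says of phase one: "It was not the intention during this phase to conduct a cross-sectional study and there was no attempt to recruit in a fully randomised way". It then offers reassurance: the 250 women are about 0.5% of South Asian women in New Zealand, and their countries of origin match the census.

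**The concern.** Prevalence and vitamin D status are population quantities, and the women screened should stand for the population named. Here one entry rule depends on vitamin D intake, which bears directly on the quantity measured. The rule has an obvious purpose in a supplementation trial. In a description of vitamin D status it removes women because of how much vitamin D they take.

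Self-selection comes on top of this, much of it through social networks. The Discussion then disowns a cross-sectional purpose, although a prevalence drawn from one screening visit answers a cross-sectional question. The sampling fraction does not bear on selection bias, and a match on country of origin does not address supplement use.

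At stake is what phase one may conclude. Followed as written, a figure for eligible volunteers would be reported as a figure for Auckland.

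**Working it through.** The article states no expected prevalence, interval or precision target for phase one, so there is no figure to reproduce. The check has four steps.

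**1. Which exclusions apply to phase one?** The supplement and calcitriol rule is applied to volunteers at large. Only the low vitamin D and metabolic criteria are labelled as additional for the trial. The plain reading is that the rule covers everyone screened.

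**2. What do the documents imply about observed prevalence?** Every woman qualifying for phase two had to be below 50 nmol/L, and the Abstract confirms that all participants were deficient. Observed prevalence in phase one is therefore at least 116/250 = 46.4%.

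**3. How far could the supplement rule alone move the estimate?** Let s be the share of otherwise eligible women removed by the rule, p the prevalence among those kept, and q the prevalence among those removed. Then

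observed − true = p − [(1 − s)p + sq] = s(p − q), which is at most s × p (when q = 0).

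The documents give neither s nor q. The values of s below, and all values of p except 46.4%, are assumptions. The last column is 1.96 × √(p(1 − p)/250), which assumes simple random sampling and serves only as a yardstick.

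| p | s = 1% | s = 2% | s = 5% | s = 10% | Half-width, n = 250 |
|---|---|---|---|---|---|
| 46.4% | 0.5 | 0.9 | 2.3 | 4.6 | 6.2 |
| 60% | 0.6 | 1.2 | 3.0 | 6.0 | 6.1 |
| 80% | 0.8 | 1.6 | 4.0 | 8.0 | 5.0 |
| 90% | 0.9 | 1.8 | 4.5 | 9.0 | 3.7 |

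Entries are the largest possible overstatement, in percentage points. If 30% of the excluded users were deficient (assumed), the entry for p = 80% and s = 5% falls from 4.0 to 0.05 × (80 − 30) = 2.5 points.

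**4. Do the other exclusions act the same way?** Not necessarily. Let d be the share excluded for renal dysfunction, systemic illness or medicated diabetes, with prevalence r. Take s as a share of the whole population here. Then

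observed − true = s(p − q) + d(p − r).

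Take p = 60%, q = 0, d = 10% and r = 70% to 80% (all assumed):

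- s = 1%: 0.6 − 1.0 = −0.4 points, to 0.6 − 2.0 = −1.4 points
- s = 5%: 3.0 − 1.0 = +2.0 points, to 3.0 − 2.0 = +1.0 point

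The sign depends on values that the documents do not give, and volunteer bias is not included.

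**The case against.** A reader might infer that the prevalence from phase one is overstated. The documents do not support that. Only the high-dose vitamin D component has an expected direction. The illness exclusions may pull the other way, and the direction of volunteer bias is not shown. Users of 1000 IU/day or less stay in. The article calls the excluded intake a prescription dose, which does not suggest common use. At s of 5% or less the effect is below the random-sampling half-width for prevalences up to 80%.

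Three further points count against a strong reading:

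- **Removal is not certain.** Supplement use was recorded on the medical history form, which was completed after the blood was drawn. No earlier screen for supplements is described, though one may have existed. Some high-dose users may have been sampled, and the text does not say how they would be counted.
- **Calcitriol is not what the assay measures.** Table 1 lists serum 25-OH vitamin D, whereas calcitriol is the 1,25-dihydroxy form. Its users cannot be presumed replete on this test.
- **The hypothesis claims only that prevalence is high.** Even with s = 10% and no excluded user deficient, the 46.4% floor would drop only to 0.464 × 0.90 = 41.8%.

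The article is also open about non-random recruitment, says that random recruitment in such a minority would be very difficult, and compares education as well as country of origin.

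All of this stands as to size and direction. It does not remove the conflict. The admission in the Discussion leaves hypothesis 1 and aim 1 unchanged and never mentions the intake-based exclusion. Nor is this detail that an article leaves to a fuller document, because the aim, the entry rule and the disclaimer are all stated in the text.

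**Conclusion.** The point holds as a mismatch between what phase one claims and what it can deliver. The aim and hypothesis name South Asian women in Auckland. The entry rule and recruitment yield eligible volunteers without high-dose vitamin D or calcitriol use, and the Discussion disclaims a cross-sectional purpose.

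Taken alone, the exclusion of high-dose users would be expected to raise the observed proportion deficient by no more than s × p. That is about 0.5 to 9 points over s = 1% to 10% and p = 46.4% to 90%. These ranges are assumptions, apart from the 46.4% floor. The conclusion also rests on reading the exclusions as study-wide, which is the plain sense of the text.

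The net bias has no established sign, so a statement that the prevalence is too high would go beyond the documents. No interval or precision claim in the article is at fault, since it makes none. The randomised comparison in phase two is unaffected.

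**What to change.** Phase one screening is reported as complete, so moving the exclusion to phase two entry is no longer possible. The remedy lies in wording and reporting.

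1. Restrict hypothesis 1, aim 1 and any prevalence conclusion to eligible South Asian women who volunteered for screening and took no more than 1000 IU/day of vitamin D and no calcitriol. Draw no Auckland-wide prevalence conclusion.
2. Bring the Discussion into line, and name the supplement exclusion there beside the non-random recruitment.
3. If the number turned away for supplement use was recorded, report it, with calcitriol users counted separately. With x deficient among 250 screened and k turned away, give the range from x/(250 + k), none of them deficient, to x/250, as deficient as the women screened. Do not fix calcitriol users as replete. For illustration, x = 200 and k = 13 (both assumed) give 200/263 = 76.0% to 200/250 = 80.0%.
4. If no count exists, say so and rely on the restricted wording. Even a recorded count would miss women who did not come forward because of the criteria.

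The cost is a few sentences and, where the count exists, one extra figure. The downside is a narrower prevalence claim. No new data are needed.

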### Setting

The study took place in Auckland, New Zealand. Auckland is New Zealand's largest city with a population of just over 1 million. The majority of South Asian immigrants settle in Auckland [24].

### Vitamin D intervention

Initial screening (phase 1 of the study) took place over a period of 9 months, commencing February 2007. See Table 1 for outcome measures and testing methods for phase 1. From the 250 women screened in phase 1, 116 qualified for phase 2, with the inclusion criteria described above. Women with FPG >7.2 mmol/L were offered a second blood test, and then withdrawn from the study and referred to their medical practitioner if the second blood test yielded similar results.

**Table 1 T1:** Outcome measures and testing methods used for phase one.

**Measure**	**Method**
**Blood analysis**	All analysed by LabPlus, Auckland City Hospital, Auckland
Fasting plasma insulin	Micro-particle enzyme immunoassay technology (MEIA), Abbott Diagnostics
Fasting plasma glucose	An enzymatic colourimetric assay; Roche Glucose reagent kit (Cat. No. 1876899)
Total cholesterol	Enzymatic colourimetric method (Roeschlau and Allain). Roche Cholesterol reagent kit (Cat. No. 1491458)
Triglycerides	Enzymatic conversion. Roche Triglycerides reagent kit (Cat. No. 1727711)
HDL-C	Homogenous enzymatic colourimetric assay. Roche HDL-Cholesterol Plus reagent kit (Cat. No. 04713214)
LDL-C	Calculated
Serum calcium	Colourimetric assay. Roche Calcium reagent kit (Cat. No. 1730240)
Serum albumin	Colourimetric assay. Roche Albumin Plus reagent kit (Cat. No. 1970909)
Serum high sensitivity CRP	Particle enhanced immunoturbidimetric assay. Roche CRPLX reagent kit (Cat. No. 03002039)
Serum parathyroid hormone	"ECLIA" electrochemiluminescence immunoassay. PTH Reagent Pack (Cat. No. 11972103122)
Serum 25 OH vitamin D	Radioimmunoassay, DiaSorin RIA kit (Cat. No. 68100E)
**Anthropmetric and clinical assessments:**	
Blood pressure	Omron HEM-907 Digital Automatic Blood Pressure Monitor
Temperature	Braun ThermoScan Pro 3000 aural thermometer
Height, weight, waist and hip circumference	ISAK anthropometry methods – ISAK level one accredited anthropometrist, Tanita electronic scales, stadiometer, Lufkin tape
**Questionnaires:**	
Dietary assessment	4-day food diary. Completed by subjects. Analysed using Foodworks 2007 (Xyris Software). Additional recipes and food lists provided by Indian dietitian
Medical and family history	Questionnaire administered following blood tests
Demographics	

One hundred and six women were recruited for phase 2, but a number were lost to the study due to becoming pregnant (n = 3), moving overseas (n = 6) perceived side-effects (n = 2), medical practitioner prescribing vitamin D (n = 3), or withdrew from study (n = 8).

The intervention consisted of a 25(OH)D_3 _supplement, 4000 international units (IU) per day, or placebo, in the form of 4 oral capsules, for 6 months. The consumption of 4000 IU 25(OH)D_3 _has been shown to be a safe and effective dose [32,33]. The active supplement was tested for 25(OH)D_3 _content by the Massey University Nutrition laboratory. The average content per dose was 4226 IU, no vitamin D was detected in the placebo. The vitamin D content will be tested again at the completion of the study to determine any degradation during storage over the period of the study.

Subjects were matched into pairs by age and BMI. Randomisation of the active/placebo capsules and allocation to pairs was performed by Blackmores using nQuery Advisor^®^, version 6.0, (Statistical Solutions, Cork, Ireland). Randomisation and allocation were fully concealed from the researchers.

Once recruited into phase two, participants were recalled for a baseline blood test prior to being given their supply of supplements. After 3 months another blood sample was taken to check for hypercalcaemia. Once the intervention was completed (6 months) participants provided one more blood sample and were weighed again. See Table 2 for outcome measures and testing methods for the intervention phase of the study.

**Table 2 T2:** Outcome measures and testing method for phase two (measured at baseline, 3 months and 6 months)

**Test**	**Method**
Blood tests As listed in table 1, plus:	
Collagen C-telopeptide (CTX) Osteocalcin (OC)	Roche Elecsys beta cross-laps Roche Elecsys 2010 Canterbury District Health Board Laboratory
Weight at baseline and 6 months	Tanita electronic scales

### Blood sampling and processing

Venous blood samples were taken by registered phlebotomists, using a sterile Vacutainer Flashback needle and needle holder between 8.30 am and 9.30 am. There is considerable circadian variability in bone markers; OC levels are increased by 20% at peak (very early morning) and CTX levels at the nadir may be half those at the nocturnal peak [20]. Accordingly, all blood samples were obtained within a consistent time period. The subjects were asked to fast overnight (at least 8 hours with no food or beverage, excluding water). Serum was used for the analysis of lipid profiles, CRP, calcium, albumin, parathyroid hormone, glucose, insulin, vitamin D. The blood was protected from light, allowed to clot for ± 30 minutes and centrifuged for 10 minutes at 2000 g at 4°C within 2 hours. For the preparation of plasma, the blood was collected in vacutainers buffered with EDTA anticoagulant, and centrifuged for 10 minutes at 2000 *g *at 4°C. For OC and CTX, plasma was dispensed and frozen within 2 hours of collection and flown to Christchurch, New Zealand on dry ice for analysis at conclusion of the study. Aliquots of serum and plasma were stored at -80°C whilst awaiting analysis.

### Questionnaires

The medical history form was completed by participants during their visit for blood tests and anthropometry. Before the participant departed the researcher checked all answers and probed any responses requiring clarification. The questionnaire included basic demographics, country of birth, length of time in New Zealand and number of years of education since age 5 years. All medication and dietary supplement use was recorded, together with tobacco, betel nut and alcohol use, menstrual status, birth control and/or HRT use, and dental history. Family history of diabetes, CVD and osteoporosis was also investigated.

The 4-day estimated dietary record was presented in an open entry booklet form with pages for recording each day's food intake and extra pages for recipes. Participants were asked to record at least one weekend or feast day. Measuring cups and spoons were provided if required. Instructions for the completion of the diary were given verbally when the participant received the diary and a list of written instructions, including examples, were provided on the first 2 pages of the booklet. The women were asked to give a detailed description of the foods eaten, if possible to give a brand name and to estimate the amounts using natural measures (e.g., pieces, slices) or household measures (e.g., coffee spoon, cup). Experienced dietitians used a standardised protocol, including a manual on household weights and measures to convert the estimated amounts into weights. All dietary records were checked for quality and completeness prior to data entry into the Foodworks 2007 programme. Additional new foods and recipes were added as required, with food composition data taken from an Indian food composition reference [34]. The recipes were adapted for individual subjects based on the ingredients that are being used in New Zealand. After data entry, each record was verified by a nutrition researcher and corrections were made if mis-interpretation or errors in data entry were found. To ensure the best possible quality of dietary data, a subset of subjects were recalled for a qualitative, in-depth interview with a dietitian assessing their 4-day food records for dietary content (quality and quantity), food types, additions to foods and drinks and recipe composition (to further clarify fat and sugar intake.)

In the present study, a 4-day estimated dietary record was chosen because of the high respondent burden and time-consuming characteristics of 7-day dietary food records. However, Nelson *et al *[35] stated that a 4-day record, randomised to cover weekday variations, seems to be the optimum. To obtain a highly accurate estimate of individual intake, a longer period would be recommended for many nutrients, especially those with a high within-person variation, but this was not feasible due to practical considerations [36].

Participants were given a free-post, pre-addressed envelope for the return of the booklet.

### Provision of results to participants

Following the receipt and analysis of the 4-day diet diary and the completion of the biochemical assays done during the screening phase, each participant received a feedback form. This contained an overview of the analysis of the diet, with particular reference to macronutrients, iron and calcium. Anthropometric measurements, blood pressure and blood results (fasting glucose, fasting insulin and lipids) were also included. Once recruitment into the trial was completed, participants not involved in the trial received notification of their vitamin D levels together with advice about supplementation where applicable.

On completion of the trial, participants will be informed of their current vitamin D status, their baseline status and if they were taking the active or placebo dose. All trial participants will be given 6 months supply of vitamin D supplements (courtesy of Blackmores), regardless of which arm of the trial they were on, upon completion of the 6-month intervention.

Newsletters were sent to all participants at intervals during the study with the goal of keeping them interested and informed.

